### Randomisation and blinding

Included participants will be allocated to the four groups by a block randomisation method, stratified for PIPJ affection in one or more of the treated fingers, and MCPJ contractures (without PIPJ affection in any of the treated fingers). The randomisation schedule will be prepared using software by an independent statistician not involved in the study. The project group will be blinded for the block size. The assignment to either the hand therapy group or the control group will be put in sealed opaque envelopes with numbers, following an order generated by the software. A list with the numbers of the envelopes will be marked when the envelopes are used. The list and envelopes will be stored in a private locked closet that is inaccessible to blinded study researchers. The envelope will be opened by the participant and a receptionist when the CCH treatment is finished. If the participant is allocated to the hand therapy group, the therapy starts at the day of the extension procedure. The surgeon is also blind to participant allocation, since the CCH treatment is finished before allocation. It is not possible for the therapist performing the hand therapy intervention to be blinded, but the person performing and managing the assessments will be blinded. The participant will be instructed not to inform the assessor of their allocation group, nor to reveal any related aspects during any of the assessments. By nature of PIPJ and MCPJ DCs, it is impossible to blind this subgroup allocation.

### Intervention

#### All participants

Participants in the two groups are all treated with a collagenase injection (i.e., CCH) and extension procedure. A needle fasciotomy is done in addition in the same procedure for a few. These will be marked, and considered as an adjustment variable in the analysis. If the extension procedure causes a wound, it is dressed, and the patient is informed on how to prevent infection. An employer sick note is provided if needed. Further intervention depends on group assignment.

#### Control group

Participants in the control group are discharged from hospital without further interventions, not even a post-treatment appointment with the surgeon. The participants in this group are neither informed of what exercises to do, nor are they to be fitted for a splint or cast. If an infection is detected or CRPS diagnosed by the personal general practitioner or the surgeon, treatment accordingly (most often hand therapy) will be initiated. The Budapest criteria for CRPS will be used [40]. If not diagnosed when meeting at the 6 weeks or 4 months re-tests, the tester will contact a MD to do it. If CRPS develops, this participant will be marked as treated with a deviation from the protocol (Fig. 1). This marking will also be done if it is revealed that a participant has received some kind of hand therapy outside of the hospital.

#### Intervention group

Hand therapy comprises the following. To ensure the best possible treatment, we will give each participant an information leaflet and a diary for them to record specific notes about their therapy experience. The information discusses oedema and scar management, correct night-time splinting, hand exercises, and everyday activities to be done for the entire post-CCH and follow-up periods. Participants of the hand therapy group are instructed by an occupational therapist experienced in hand therapy for DC at the day of the extension procedure. An extension splint is moulded, and night-time splinting begins at this time. Instructions on how to do hand exercises are also given. Specifically, participants are asked to and instructed how to perform the daily activities listed in the Canadian Occupational Performance Measure (COPM). Depending on the patient’s needs and progress of oedema, scarring, proper splint adjustments, ROM, and mastering everyday activities, the timing and the amount of therapy sessions will vary individually. The participants will at least be seen at 4 and 6 weeks, but mostly they will also be seen at 1–2 weeks post CCH-treatment. The participants will be instructed in how to do exercises, use their hand in daily activities as exercise and treat their scar or oedema on their own. Use of the routine night-time splint will be discontinued at 4 months. Some participants might voluntarily choose to use it beyond the 4 months; this is noted. Therapy sessions might continue after 4 months, as it sometimes takes time to elongate structures surrounding the joints. If there is a persistent rest-contracture, this is noted. The therapist and participant end hand-therapy sessions when no improvement of joint extension is achieved for two sessions with 2 months apart, or if full ROM is achieved, whichever comes first. The intervention group is free to contact the study’s occupational therapist at any time during the trial.

#### Oedema and scar management

Oedema treatment is standard, and comprises rest and elevation of the hand in combination with movement of the whole arm and use of the affected hand in everyday activities. Compression achieved with an elastic self-adhesive bandage or with a oedema glove is recommended for 12 h per day for prolonged oedema (i.e., lasting more than 72 h) as long as it persists.

Every laceration leaves a scar. If present, scar treatment is standard, comprising application of pressure through a splint or paper tape, and sometimes includes silicone treatment [23]. If the scar is hard or hypertrophic, use of a splint together with a silicone sheet is recommended [26–28]. Scar and oedema treatment is recommended for 12 h per day for 2 months or more, if needed [41].

If needed for oedema management, exercises are performed as long as the oedema persists, and include the following:
move arms up above the head and down againmake a fist and stretch the fingers out (Figs. 2 and 3)keep the arm elevated by resting it on the chest when walking about or on a pillow for the first 2–3 days (inflammation-phase)

**Fig. 2 Fig2:**
[figure not shown]
Make a fist

**Fig. 3 Fig3:**
[figure not shown]
Stretch out the fingers

#### Splinting

The splint is an individually moulded volar splint made of thermoplastic. It is custom-formed to accommodate the treated finger(s) and the neighbouring finger, with the MCPJs slightly bent and PIPJs extended (Figs. 4 and 5). As the hand is sedated at the time the splint is moulded, we do not know whether wearing the splint will be painful. When the splint is being fitted, too much pressure on the fingers and excessive tension at the possible wound site must be avoided. When the wound has healed and as pain thresholds permit, the splint can be remoulded as appropriate. Elastic Velcro is adhered dorsally to prevent the splint from twisting and turning, and is sufficiently wide to produce light pressure for elongating structures, if necessary. Participants are encouraged to contact the therapist for splint adjustments, if something prevents them from wearing it. Precautions will be specifically guided by patient-reported pain, as pain is indicative of possible micro tears in hand tissues, leading to scarring and more contractures. If the PIPJ contracture is severe (≥40 degrees) post-CCH, an even more-targeted splint for the specific joint will be constructed when the possible wound is sufficiently healed – a finger Gutter splint” (Figs. 6 and 7) or a three point finger splint (Figs. 8 and 9).

**Fig. 4 Fig4:**
[figure not shown]
Night splint volar side

**Fig. 5 Fig5:**
[figure not shown]
Night splint dorsal side

**Fig. 6 Fig6:**
[figure not shown]
Finger gutter splint, volar side

**Fig. 7 Fig7:**
[figure not shown]
Finger gutter splint, dorsal side

**Fig. 8 Fig8:**
[figure not shown]
Finger three-point splint volar side

**Fig. 9 Fig9:**
[figure not shown]
Finger three-point splint dorsal side

#### Exercises

Patients are instructed to perform the exercises at home several times a day for short sessions, completing 10 repetitions for each exercise.

Hand exercises, if hand function is impaired:
make a fist and stretch out the fingers to engage finger movement (Figs. 2 and 3)isolated exercises for the specific joint(s) (Fig. 10, 11 and 12)

**Fig. 10 Fig10:**
[figure not shown]
Isolated exercise for DIPJ

**Fig. 11 Fig11:**
[figure not shown]
Isolated exercise for PIPJ

**Fig. 12 Fig12:**
[figure not shown]
Isolated exercise for MCPJ

Hand exercises, if the PIPJ is involved:
flexion of the DIPJ with the PIPJ held in extension to lengthen the oblique retinacular ligaments (Fig. 10)extension of the PIPJ and DIPJ with the MCPJ blocked in flexion (Fig. 13)

**Fig. 13 Fig13:**
[figure not shown]
Extension of the PIPJ and DIPJ with the MCPJ blocked in flexion

#### Everyday activities

The therapy sessions will focus on activities listed in each patients’ COPM. The activities will be written in the diary to aid the patient’s memory. The therapist will guide the patients in how to use these activities as exercise, and will motivate the patients by explaining that performing rote exercises, in combination with other exercises through meaningful activities, produces better results [40].

### Treatment adherence

Patients in the intervention group will receive written instructions containing all the information about their treatment. They will meet the therapist individually as often as necessary, and for a minimum of three sessions: (1) at the day of the extension procedure; (2) within 4 weeks; and (3) at 6 weeks. They are free to contact the therapist if needed. This follow-up is designed to encourage treatment adherence.

### Outcome measures

Recommendations for assessing treatment progress for DC will be used [42, 43]. These include a combination of generic patient-reported outcome measures (PROM), a disease-specific questionnaire, a physical measure of active and passive individual joint ROM, and grip strength, using standardised protocols for DC assessment. An overview of the measures used is presented in Table 1 together with the schedule of when they are performed. Differences in performance parameters between the two groups will be evaluated. Subgroups will be similarly evaluated. Patient performance of and self-satisfaction with performance of everyday activities 1 year after CCH treatment will be the main outcome of interest.

**Table 1 Tab1:** Schedule of enrolment, interventions, and assessments of patients with Dupuytren’s contracture

	Enrolment	Baseline tests	CCH treatment	6 weeks follow up	4 months follow up	1 year follow up
ENROLEMENT:						
Eligibility screen	X					
Informed consent	X					
Randomisation			X			
INTERVENTIONS:						
Hand therapy			X	X	X	
No hand therapy			X	X	X	X
ASSESSMENTS:						
Demographic and medical variables		X		X	X	X
Main outcome						
Everyday activities: COPM		X		X	X	X
Secondary outcomes						
Range of motion: Goniometer		X	X	X	X	X
Everyday living activities: URAM scale		X		X	X	X
Grip force: Jamar dynamometer		X		X	X	X
Pain: VAS		X		X	X	X
Cold hypersensitivity: Yes/no		X		X	X	X
Sick leave: Yes/no		X		X	X	X
Satisfaction with change in hand function: PGIC					X	X

### Primary outcome measure: Canadian model of occupational performance

The Canadian Occupational Performance Measure (COPM) is a client-centred tool, with which individuals identify and prioritise everyday issues that restrict or impact their performance of everyday living activities [44]. The Norwegian version of the COPM will be used [45]. The COPM is reliable [46], has good construct validity for DC [47], as well as criterion responsiveness [48]. It is a relevant instrument for the population of DC sufferers and captures performance problems that may be missed by other tests [47].

This self-perception of performance and satisfaction with performance is tracked over time by the tool. To optimise the relevance of the COPM in this study, participants are asked to identify activity limitations caused as a result of their DC. Participants rate the importance of each activity on a scale from 1 to 10, and they select a maximum of five activity limitations that they feel are the most important activities they want to improve. The participants evaluate each activity with regard to their actual performance and satisfaction with their performance on a scale from 1 to 10; higher values indicate better performance or greater satisfaction. The mean total performance score and satisfaction score will be calculated over the chosen activities. We deemed a change in score of 2 as a clinically important change, a value indicated in the literature for the COPM [44].

At each of the follow-up assessments, participants will rate their current performance and satisfaction with their performance of each of the five activities that they identified at baseline. Change scores are calculated using the previous scores and the current ones.

### Secondary outcomes

#### Unité Rhumatologique des affections de la Main (URAM) scale

To better compare the results of this proposed trial on DC with other studies, and to examine participants’ performance of predefined disease-specific activities, we will use the Norwegian version of the Unité Rhumatologique des Affections de la Main (URAM-N) scale [49]. Performance of nine predefined activity limitations is evaluated on six different degrees of performance. With the URAM-N, a maximum score of 45 is possible, indicating the worst possible condition. The original version of the URAM scale has strong convergence with the Tubiana scale (contractures of the joints) and self-assessed disability measured with a visual analogue scale (VAS) [3]. The clinimetric properties for the Norwegian scale have not been tested yet.

#### Range of motion (ROM)

In the majority of research on DC treatments, ROM is the primary outcome variable. In the present trial, group differences in mean change of ROM (active flexion and active/passive extension of each treated joint) will be evaluated. DC recurrence rates will also be evaluated in the four groups. We define a successful result as (1) a joint that achieves an extension to 0–5 degrees of full extension, and (2) a clinical improvement of more than 50% reduction of the original contracture [12]. We adopted recommendations to improve ROM measuring and reporting [39, 50]. A Rolyan goniometer with a precision of five-degree intervals (range, 0–180 degrees) will be used to measure ROM, as it is the established ROM-measuring tool routinely used in a clinical context. Only treated joints will be measured for ROM.

The Swedish Hand Surgical Quality National Register (HAKIR) reached a consensus on how to measure ROM with a goniometer [51]. This method will be followed, and in addition, we will measure with the elbow resting on a table, hand up, and wrist in neutral position. MCPJs will be both flexed and then extended when measuring PIPJ extension. Active flexion and both passive and active extension of each treated joint will be measured separately. The results will be tabulated, as recommended by Kan et al. [39]. Extension deficit is marked with a minus sign, full extension and hyperextension is defined as zero degrees. We define DC recurrence as an increase in treated-joint contracture at the one-year follow-up of at least 20 degrees compared to the six-weeks follow-up measurement [39].

Following the COSMIN criteria [52], one systematic review found a limited level of evidence for an acceptable reliability in the dorsal measurement method of goniometry assessment of the finger joints, and an unknown level of evidence for the measurement error [53].

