### Participants

This study is currently recruiting participants (study start date: 10th of April 2018). Adult men and women who have had their DC treated with one CCH injection in one-tree fingers with joints summarised to ≥30° extension deficit are eligible. Patients can participate only once. Reasons for exclusion are as follows:
having previous treatment for DC in the same finger being considered for the interventionhaving previous surgery or a major injury that affects the same fingers movementhaving complex regional pain syndrome, infection, or an allergic reaction to the CCH before randomisationhaving a tendon or ligament rupture in the hands before randomisationa patient incapable of complying with a therapy program due to cognitive or language challenges.

Activity performance and satisfaction are affected by capacity of both hands. Therefore, participation in the study is appropriate only once. If any of the included participants receive DC treatment in the unparticipating hand, or for other fingers of the experimental hand, during the present trial, this will be noted and considered as an adjustment variable in the analysis. Previous injury or DC treatment would undoubtedly cause changes in the connective tissue and would likely confound the results of our study. Participants who develop complex regional pain syndrome (CRPS) or infection, diagnosed by a doctor, must undergo hand therapy regardless of whether it affects hand function severely. This will be considered in the analysis as an adjustment variable.

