#### Additional questions

Basic demographic information will be collected. Indications for treatment in other fingers in the same hand or in the other hand will be recorded at baseline and re-assessed at each follow-up. We will ask the participants whether they are sensitive to cold and about sick leave, both at baseline and at the follow-ups. Difficulties with oedema and scarring will be queried at the follow-ups. The participants in the intervention group will record in a diary if they have a wound, scar, or swelling; whether they used the splint and how much; and whether they used the COPM activities as exercise. The diary will be retrieved by a secretary at the four-month follow-up and the data analyst will analyse these data after the final follow-up at 1 year.

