## Discussion of methodological limitations and strengths

All clinical trials require completely transparent protocols [61]. By using the SPIRIT recommendations for minimum relevant protocol items, we achieved this goal of transparency. This paper describes the study design for an RCT investigating the effects of hand therapy, or lack of it, on patients who have undergone CCH treatment for DC. The study is also designed to determine whether differences exist in the outcome measures of patients with DC of the PIPJ involved or of only the MCPJ. The design is not optimal, as patients and therapists cannot be blinded to the treatment modality. This is a common problem in clinical studies. However, the therapist assessing the participants’ performance and satisfaction, the surgeon, and the data analyst will be blinded to the treatment modality.

In drafting our research plan, we considered recommendations in the empirical literature on DC. It is impossible to fully control some factors or issues. For example, the presentation of DC varies considerably, making each DC case unique. Thus, patients will respond differently to the CCH treatment and will thus require different therapeutic interventions to address their unique complaints. Also, as DC is a chronic disorder, the disease itself remains active even after treatment and thus contractures may continue to occur. Another issue that we cannot control is the structural status or integrity of tissues surrounding the affected joint. Those structures may be so stiff that it would be impossible to fully straighten the affected joint. These issues make research on DC treatments and rehabilitation challenging. Our study, however, has attempted to control for some of these variations by incorporating two subgroups, one comprising patients with PIPJ contractures and the other comprising patients with only MCPJ contractures. We surmise that one of the subgroup of patients may require more intensive hand therapy than the other.

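### Recurrence is scored from the change in joint angle between 6 weeks and 1 year, with no rule for a study joint that is re-treated in between

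*Protocol article*

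**What the plan says.** In the protocol article, the section on range of motion gives the rule: "We define DC recurrence as an increase in treated-joint contracture at the one-year follow-up of at least 20 degrees compared to the six-weeks follow-up measurement". It plans a comparison on that rule: "DC recurrence rates will also be evaluated in the four groups". Success is also defined by angle: "We define a successful result as (1) a joint that achieves an extension to 0–5 degrees of full extension", together with "a clinical improvement of more than 50% reduction of the original contracture". Neither definition mentions a further procedure on the joint, and the success sentence names no time point.

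Three places say which later treatment is tracked:

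- **Participants:** it covers patients who "receive DC treatment in the unparticipating hand, or for other fingers of the experimental hand, during the present trial, this will be noted", and makes this an adjustment variable.
- **Additional questions:** "Indications for treatment in other fingers in the same hand or in the other hand will be recorded at baseline and re-assessed at each follow-up".
- **Control group:** after describing the marking of CRPS as a deviation, it adds: "This marking will also be done if it is revealed that a participant has received some kind of hand therapy outside of the hospital".

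The section on all participants also marks needle fasciotomy done in the same session as the extension procedure. Table 1 schedules demographic and medical variables at every follow-up without listing what they contain. The statistical analysis section states intention to treat and gives no rule for re-treatment.

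**The concern.** The protocol expects contractures to return. Its discussion says "the disease itself remains active even after treatment and thus contractures may continue to occur", and the enrolment section gives detection of recurrence as one reason for the 1-year visit. A second procedure on a study joint within the year is therefore foreseeable. Such a procedure changes the very angle on which recurrence is scored.

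A joint that re-contracted and was successfully re-treated can then look the same at 1 year as a joint that never re-contracted. Because re-treatment follows from a poor result, the misclassification depends on outcome. It may also differ by arm. Controls are discharged with no surgeon appointment, while therapy patients are seen repeatedly and may contact the study therapist at any time. At stake is the planned comparison of recurrence rates and, if success is judged at 1 year, of success rates.

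**Working it through.** **The plan's own figure.** Recurrence and success have no stated rate, power or sample size. The only sample size is for COPM (difference 1.0, SD 2.0, two-sided 5%, power 0.80):

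- Normal approximation: n = 2 × (1.96 + 0.8416)² × 2.0² / 1.0² = 62.8, so 63 per group.
- t-test: 63.8, so 64 per group, with power 0.801.
- After 20% loss: 64 / 0.8 = 80 per group.

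The stated 64 and 80 reproduce. Neither depends on the recurrence rule.

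**Applying the rule.** A joint is recurrent if its deficit at 1 year minus its deficit at 6 weeks is at least 20 degrees. The example angles are assumed:

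| Course after a 5-degree deficit at 6 weeks | Deficit at 1 year | Change | Scored as |
|---|---|---|---|
| Worsens to 45, left alone | 45 | +40 | recurrent |
| Worsens to 45, re-treated, good result | 10 | +5 | not recurrent |
| Worsens to 45, re-treated, poor result | 25 | +20 | recurrent |

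If the re-treated joint instead measures 5 degrees at 1 year and began with an assumed 40-degree contracture, the reduction is (40 − 5) / 40 = 87.5%. Both success criteria are then met, provided that success is judged at 1 year. Table 1 also schedules goniometry at 4 months, but the recurrence rule does not use that measurement.

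**Possible size.** All rates here are assumptions. Each re-treated joint is taken to measure less than 20 degrees worse at 1 year than at 6 weeks. Observed rate = true rate × (1 − share of recurrent joints re-treated).

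| True rates, control / therapy | Share re-treated, control / therapy | Observed rates | Difference, true → observed (points) |
|---|---|---|---|
| 20% / 10% | 25% / 25% | 15% / 7.5% | 10 → 7.5 |
| 20% / 10% | 50% / 50% | 10% / 5% | 10 → 5 |
| 20% / 10% | 50% / 25% | 10% / 7.5% | 10 → 2.5 |
| 20% / 10% | 50% / 0% | 10% / 10% | 10 → 0 |
| 20% / 10% | 0% / 50% | 20% / 5% | 10 → 15 |
| 30% / 15% | 50% / 50% | 15% / 7.5% | 15 → 7.5 |
| 30% / 15% | 50% / 0% | 15% / 15% | 15 → 0 |

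With equal shares the absolute difference shrinks by the share re-treated, but the risk ratio stays at 2.0 (20/10 = 15/7.5 = 10/5). Precision still suffers. For true rates of 30% and 15% with 64 independent units per arm, power is 0.53 with no re-treatment, 0.40 with a quarter re-treated and 0.27 with half re-treated. With unequal shares the relative effect moves as well, in either direction.

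**The case against.** The best case for leaving the text alone has five parts.

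1. **Re-treatment may be recorded anyway.** Table 1 lists medical variables at each follow-up, and a journal article condenses a fuller protocol. This stands in part: a reader might infer that re-treatment of the study finger goes unrecorded, and the article does not establish that. But where it names the DC treatment to be noted, it leaves out the study finger, and its recurrence definition would ignore such a record even if one existed.

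2. **The definition is an adopted consensus.** The discussion explains that differing definitions change reported recurrence rates, so comparability with other studies has value. This stands as a reason to keep the angle-only rate as well. It does not settle how a joint altered by a second procedure should be scored in this trial.

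3. **The event may be rare.** Patients come from a waiting list and controls have no routine surgeon visit, so re-contracture, referral and a second procedure must all fall within the year. This stands: the documents give no rate.

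4. **The bias need not favour one arm.** A reader might infer that the between-arm difference must shrink. The documents do not support that. Equal re-treatment leaves the risk ratio unchanged, and more re-treatment among therapy patients would exaggerate the benefit.

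5. **Counting every re-treated joint as recurrent would create a new error.** The intervention section anticipates contracture that persists after treatment. A joint re-treated for that reason never worsened by 20 degrees and is not a recurrence. This stands, and the fix has to separate the two cases.

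**Conclusion.** The point holds in a limited form. The recurrence rule, read with the list of treatments to be noted, scores a study joint as non-recurrent if it re-contracts, is re-treated before 1 year and then measures less than 20 degrees worse than at 6 weeks. This is a defect in a rule the article itself fixes, not a detail left to another document.

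Two stronger readings are tempting:

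- **Every re-treated joint escapes being counted.** The text does not support this, because a re-treatment with a poor angle at 1 year is still scored recurrent.
- **The worst outcomes are coded as the best.** This needs a final deficit of 0–5 degrees, more than 50% reduction, and success judged at 1 year, which the success sentence does not say.

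The effect falls on secondary outcomes. The hypotheses concern COPM performance and satisfaction and the role of joint involvement. The COPM analysis and sample size do not use the recurrence rule, although a patient's 1-year COPM score would reflect any second procedure. The amount and direction of bias are unknown, and the tabulated figures only show a range under assumed rates. The change is worth making because it is cheap and because a procedure and date not collected during follow-up may be hard to recover later.

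**What to change.** **Recording (Participants section).** Extend the noting of DC treatment during the trial to the study finger or fingers, in both arms. Record the date, the reason and the last angle before the procedure. Extend the noting only, not the covariate adjustment: re-treatment of a study joint can itself result from the allocated treatment.

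**Definitions (range of motion section).**
- Count a study joint re-treated for re-contracture after the 6-week visit as recurrent, and as not successful at 1 year, whatever its 1-year angle.
- Report joints re-treated for residual contracture that never worsened separately, as not successful but not as recurrent.
- State the time point at which success is judged.

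**Analysis.** Report the number re-treated by arm. Keep the angle-only recurrence rate as a sensitivity analysis, for comparison with other studies. Keep COPM as observed under intention to treat.

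**Cost.** One added follow-up item and a few sentences in the definitions. The downside is that re-treatment partly reflects patient and surgeon choice and is a softer event than an angle; the sensitivity analysis shows how much that matters. The change concerns recording and analysis only, not whether or when a joint should be re-treated.
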